## Abstract

**Background:**

Myasthenia gravis has a variable disease course. Early identification of patients with a highly active disease is crucial to prevent myasthenic exacerbations and crisis, necessitating more aggressive immunotherapy. However, no biomarkers currently exist to identify patients at risk for highly active disease course.

**Objective:**

The PROGNO-MG study aims to identify blood-based biomarker signatures associated with a highly active disease course in immunotherapy-naïve patients with acetylcholine-receptor-antibody positive (AChR^+^) generalized Myasthenia gravis (gMG).

**Methods:**

This is an investigator-initiated prospective, multicentric, observational study. Seventy newly diagnosed immunotherapy-naïve AChR^+^ gMG patients will be enrolled and followed up for 24 months. Blood samples and clinical data will be collected biannually. Biomarkers (calprotectin, neurofilament light chain, ITIH3, complement activation, kappa free light chains, and exploratory proteome-analyses and immune cell phenotyping) will be measured and their association with clinical outcomes will be evaluated.

**Perspective:**

The results will provide evidence for prognostic biomarkers, supporting risk stratification and early individualized treatment for AChR^+^ gMG patients.

**Trial registration:**

The study is registered in the German clinical trial register (DRKS00035457).

## Introduction

Myasthenia gravis (MG) is a rare chronic autoimmune disorder marked by muscle weakness associated with fatigability. The clinical course varies widely, ranging from only ocular manifestations to generalized MG (gMG) with recurrent myasthenic crisis characterized by respiratory failure. Despite standard of care, disease burden remains high in many patients, especially with highly active disease course [1]. Consequently, novel therapeutic approaches have emerged, including C5 complement inhibitors and neonatal Fc receptor inhibitors, which have been approved as add-on therapies for patients with highly active acetylcholine-receptor antibody positive (AChR^+^) gMG and in the case of the FcRn inhibitor rozanolixizumab for muscle-specific kinase (MuSK) antibody-positive individuals [2].

The underlying pathophysiology involves autoantibodies targeting antigens at the motor endplate of the neuromuscular junction. IgG-antibodies directed against the acetylcholine-receptor are detected in approximately 80% of all patients, while antibodies against MuSK occur in 3-5% and lipoprotein receptor-related protein 4 (LRP4) account for approximately only 1% of patients. Notably, 10-15% of all patients remain seronegative [1, 3]. Antibody testing is crucial for establishing the diagnosis of MG, as it also influences treatment decisions, such as the consideration of thymectomy and the choice of immunotherapy [3]. However, the role of antibody levels as a biomarker to further guide treatment remain inconclusive and are not useful as a prognostic marker to identify patients at risk for a highly active disease course requiring escalation of immunotherapy to prevent myasthenic crisis or exacerbation [4]. In recent years, several other prognostic biomarkers have been proposed. Serum calprotectin and serum neurofilament light chain levels were shown to be significantly increased in MG patients, however, mild correlation to disease activity in a large patient population was only seen for calprotectin [5, 6]. Recently, proteomics-based approaches were useful in identifying single potential biomarker, e.g., inter-alpha-trypsin inhibitor heavy chain H3 (ITIH3) in AChR^+^ patients that correlated well with clinical disease activity [7], as well as clustering for proteome signatures that predict treatment response in subsets of MG patients [8]. In addition, comparative proteomic analyses have been useful in identifying additional candidate biomarkers to distinguish AChR+ MG from other neuroinflammatory diseases, further supporting the utility of proteomics-based approaches for biomarker discovery in MG [9]. Moreover, immune cell phenotyping and complement activation profiles have shown promise in exploratory studies [10–12]. Importantly, most existing biomarker studies in MG have been cross-sectional or included treatment-exposed populations, limiting their prognostic applicability. In this study, we seek to evaluate the prognostic value of these proposed biomarkers in a subset of AChR^+^ gMG patients with a highly active disease course, potentially supporting clinical decision-making and personalized care.

## Methods

### Aim of the trial

PROGNO-MG hypothesizes that gMG patients who will progress to a highly active disease variant show a distinct immune and biomarker signature prior to progression compared to patients showing a moderate disease course. This might enable personalized treatment decision in the future.

### Study description and study design

PROGNO-MG is a prospective investigator-initiated, multicentric, non-interventional observational cohort study. The study is conducted across specialized MG centers in Germany. All enrolled patients will be followed for 24 months with standardized assessments every 6 months (Fig 1). PROGNO-MG is an observational study and participation will not impact on treatment choices or concomitant care.

**Fig 1. Fig1:**
[figure not shown]
PROGNO-MG Study flow chart. Biannual study visits are planned for acetylcholine-receptor antibody positive (AChR^+^) generalized Myasthenia gravis (gMG) patients. Progression to a highly active disease course will lead to a drop-out and an unscheduled visit with clinical assessment, blood sampling and patient-reported outcome (PRO) assessment

### Eligibility criteria

Inclusion criteria are as following:Written informed consentAge 18-75 yearsNewly diagnosed AChR^+^ gMG (diagnosis <12 months) with one of the following: response to an acetylcholinesterase inhibitor or decrement after repetitive serial stimulation (outside M. orbicularis oculi) or increased jitter in single-fiber EMGImmunotherapy-naïve (corticosteroids and symptomatic therapy with pyridostigmine allowed)

Exclusion criteria:Prior immunosuppressive therapy (including azathioprine, mycophenolate mofetil, methotrexate, cyclosporine, tacrolimus) or targeted escalation therapies (including C5-inhibitor, FcRn-inhibitor, B-cell depletion like rituximab)Prior thymectomy or thymoma-associated MGRecent (≤3 months) use of intravenous immunoglobulins, plasma exchange, or immunoadsorption

### Arms and interventions

This prospective observational study will enroll 70 patients with gMG. Based on disease activity trajectories, we anticipate 10-15% of the participants will develop highly active disease within an observation period of two years. We will compare these individuals to the remaining 85-90% exhibiting a moderate disease course to identify associated biomarker signatures. Immunotherapy-naïve was defined as absence of prior treatment with long-term immunosuppressive or targeted immunotherapies. Corticosteroid treatment was permitted, as it represents standard first-line therapy in newly diagnosed generalized MG, and withholding treatment for study inclusion would not be ethically appropriate.

According to the German guideline for diagnosis and treatment of myasthenic syndromes, a highly active gMG, including so-called therapy-refractory MG were defined as [3]:A moderate to high MGFA classification (≥ MGFA IIb) and/or at least two recurrent severe exacerbations or myasthenic crises requiring therapeutic intervention (e.g. IVIG, plasma exchange, or immunoadsorption) within one year of diagnosis, despite adequate disease-modifying and symptomatic treatment; **or**Persistent, functionally relevant symptoms (≥ MGFA IIa) along with at least one severe exacerbation or myasthenic crisis within the past year, despite adequate disease-modifying and symptomatic treatment; **or**Persistent, functionally relevant mild to moderate symptoms (≥ MGFA IIa) for more than two years, despite adequate disease-modifying and symptomatic treatment.

Statistical power was calculated to detect hazard ratios ≥3 for biomarkers predicting disease progression.

Patients will undergo a standardized assessment at baseline and every 6 months for overall 24 months (Table 1):Clinical assessments (e.g. MGFA [13], QMG [14], MGC scores [15]), including current immunotherapy and symptomatic therapy with reported side effects, thymectomy, comedications and comorbiditiesPatient-reported outcomes (MG-ADL [16], MG-QoL15r [17], Neuro-QoL Fatigue [18], Beck Depression Inventory [19], PASS [20], SSQ [21])Sampling for biomarker analysisBiomarker testing: calprotectin, neurofilament light chain, ITIH3, complement activation profiles, kappa free light chainsExploratory analyses: proteomics and immune cell phenotyping

**Table 1 Tab1:** Summary of standardized assessment

Assessment	V1 (baseline)	V2 (6 months)	V3 (12 months)	V4 (18 months)	V5 (24 months)	Drop-out before regular study end
Clinical parameters (height, weight, ethnicity, family history, substance history, vaccination status)	X					
Clinical scores (QMG, MGFA, MGC)	X	X	X	X	X	X
Thymectomy status	X	X	X	X	X	X
Survey on adverse events		X	X	X	X	X
MG-specific therapy	X	X	X	X	X	X + planned intensified therapy
Comorbidities	X	X	X	X	X	X
Concomitant therapies	X	X	X	X	X	X
Patient reported outcomes (MG-ADL, MG-QoL15r; Neuro-Qol fatigue score, BDI, PASS, SSQ)	X	X	X	X	X	X
Biosampling (blood sampling)	X	X	X	X	X	X

MG = myasthenia gravis; QMG = quantitative myasthenia gravis score; MGFA = myasthenia gravis foundation of America clinical classification; MGC = myasthenia gravis composite score; MG-ADL = myasthenia gravis activities of daily living; myasthenia gravis quality of life revised; Neuro-Qol fatigue score = quality of life in neurological disorders; BDI = Beck´s depression inventory; PASS = patient acceptable symptom state; SSQ = single simple question

At baseline additional demographic data will be collected, including sex, age, body mass index, vaccination status and potential substance abuse. Unscheduled visits will be conducted in the event of disease exacerbations.

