### Statistical analysis

The study is exploratory, and the number of cases is not sufficient to answer confirmatory questions. The study only serves to discover indications of possible correlations between biomarker levels and outcomes. Overall patient sample size is estimated based on a 10-15% of gMG patients progressing to a highly active disease course within two years for this explorative study [2, 3]. The sample size was calculated using a Cox regression for a *log Hazard Ratio on a covariate* with a standard deviation of 1. A sample size of n=70 provides a power of 81% for a regression coefficient of ≥ 1.099 (corresponding to a hazard ratio of ≥3) at a two-sided significance level of 5%. The calculation assumes an event rate of 12% (n = 8-9). The estimation accounts for potential confounding covariates in a multiple regression analysis, assuming an R^2^ of 0.2. The software nQuery Advisor 9 was used for sample size estimation. Cox proportional hazards models will be used to assess the relationship between biomarkers and disease progression. Time-dependent covariates and potential confounders will be adjusted in Cox regression models. Proteomic data will be analyzed using false discovery rate adjustments for multiple testing. Statistical analysis will be performed by the Institute of Biometry and Clinical Epidemiology Charité - Universitätsmedizin Berlin.

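### Two of the three event criteria do not fit 24 months of follow-up from an enrolment up to 12 months after diagnosis, so the lag to enrolment changes the routes to the event and their timing

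*Protocol article*

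**What the plan says.** The protocol article (Arms and interventions) defines highly active disease by three criteria joined by 'or', each with its own clock:

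- **Criterion 1:** MGFA IIb or higher and/or at least two severe exacerbations or crises, "within one year of diagnosis, despite adequate disease-modifying and symptomatic treatment".
- **Criterion 2:** persistent symptoms at MGFA IIa or higher with at least one severe exacerbation or crisis in the past year.
- **Criterion 3:** persistent symptoms at MGFA IIa or higher "for more than two years, despite adequate disease-modifying and symptomatic treatment".

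The primary endpoint (Outcome measures) is development of this state requiring escalation. Eligibility criteria admit patients diagnosed less than 12 months earlier who have had no long-term immunosuppressive or targeted therapy; corticosteroids are allowed. Under Study description and study design, "All enrolled patients will be followed for 24 months", and Table 1 ends regular visits at V5, month 24.

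Statistical analysis plans Cox regression and assumes a 12% event rate (8-9 events): "A sample size of n=70 provides a power of 81% for a regression coefficient of ≥ 1.099".

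**The concern.** The entry window, the follow-up length and the event definition are all printed, and they do not fit together. Criterion 1 closes at a point that falls earlier in follow-up the later a patient enrols. Criterion 3 needs more than 24 months in a study that observes exactly 24, and its start is not given.

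Time since diagnosis at V1 therefore governs which routes to the event are open and when. It may also be related to biomarker level, for example through disease stage or corticosteroid exposure before entry. If so, a biomarker hazard ratio could partly reflect when the patient was enrolled. If not, patients with different routes open are still pooled in one risk set, which can dilute the hazard ratio. With 8-9 events, a few that are shifted or lost matter.

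**Working it through.** **Inputs** (protocol article). From Statistical analysis: N = 70; event rate 12%; log hazard ratio 1.099 for a covariate "with a standard deviation of 1"; R² = 0.2; test "at a two-sided significance level of 5" per cent. From Eligibility criteria: lag d from diagnosis to enrolment, 0 to under 12 months. From Study description and study design: follow-up of 24 months from enrolment.

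**Step 1: the plan's own figure.** For a continuous covariate in Cox regression,

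power = Φ( √(N × event rate × SD² × (1 − R²)) × log HR − 1.96 ).

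Expected events are 70 × 0.12 = 8.4. Then √(8.4 × 0.8) × 1.099 − 1.96 = 2.592 × 1.099 − 1.96 = 0.889, and Φ(0.889) = 0.813. The stated 81% is reproduced.

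**Step 2: the window each criterion leaves inside follow-up.** Follow-up covers months d to d + 24 after diagnosis.

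- Criterion 1, where the one-year limit applies: open from d to 12, that is 12 − d months.
- Criterion 3 counted from diagnosis (an assumption, since no start is stated): can first be exceeded after study month 24 − d, leaving d months.
- Criterion 3 counted from treatment begun at or after V1: more than 24 months cannot elapse by V5, leaving 0 months.
- Criterion 2: the past year rolls with the patient, leaving all 24 months.

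| Lag d (months) | Criterion 1 open (months) | Criterion 3 from diagnosis: after study month | Criterion 3 months left | Criterion 2 open (months) |
|---|---|---|---|---|
| 0 | 12 | 24 | 0 | 24 |
| 3 | 9 | 21 | 3 | 24 |
| 6 | 6 | 18 | 6 | 24 |
| 9 | 3 | 15 | 9 | 24 |
| just under 12 | about 0 | about 12 | about 12 | 24 |

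The lag acts in opposite directions on criteria 1 and 3.

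**Step 3: what the wording leaves open.** In criterion 1, the 'and/or' does not show whether the one-year limit binds only the exacerbations or also the MGFA IIb part. If only the exacerbations, the MGFA IIb route is open throughout. In criterion 3, the clock could start at symptoms, diagnosis or treatment. The condition that symptoms persist despite adequate disease-modifying treatment points to treated time. In patients without earlier long-term immunosuppression, that is time before V1 only if earlier corticosteroids count, which the article does not say.

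**Step 4: sensitivity of power to unreachable events.** The article does not say how the expected events divide among the criteria, so the loss is an assumed range, put into the Step 1 formula.

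| Share of expected events unreachable (assumed) | Events left | Power |
|---|---|---|
| 0% | 8.4 | 81% |
| 10% | 7.6 | 77% |
| 20% | 6.7 | 72% |
| 30% | 5.9 | 66% |
| 50% | 4.2 | 52% |

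**The case against.** **Criterion 2 keeps the event open to everyone.** A reader might infer that enrolment date decides whether a patient can have the event at all. The document does not support that. A patient with persistent symptoms at MGFA IIa or higher who has a severe exacerbation after month 12 from diagnosis still qualifies through criterion 2, which asks for one exacerbation where criterion 1 asks for two. Late enrolment removes a route, not the endpoint. This stands and limits the point.

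**Only criterion 1 names diagnosis.** It would be wrong to say that all the criteria run from diagnosis. If criterion 3 runs from treatment begun at V1, it is unreachable whatever the lag. This stands too, but it does not rescue criterion 3. From diagnosis it is partly observable, and from treatment begun at or after V1 it is not observable.

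**The 12% may already be a two-year rate.** Arms and interventions and Statistical analysis both refer to progression within two years. A reader might infer that the rate assumes all criteria are available to everyone, or that part of the 8-9 events cannot occur in the study. Neither is stated, and the sources for the rate are not at hand. What remains is that the article does not tie the rate to the criteria that can be met between V1 and V5.

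**Time origin and covariates belong in the analysis plan, and the study is exploratory.** The article promises adjustment for potential confounders and allows R² = 0.2 for it. Its silence on the Cox time origin is no fault by itself. The mismatch, however, lies in rules the article does print, and it affects exploratory estimates as well. The exploratory aim does lower the severity.

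**Conclusion.** The point holds in limited form and should be fixed. Criterion 1, where its limit applies, is open for 12 − d months of follow-up (12 down to almost none). Criterion 3 has no stated start: it is observable for d months if counted from diagnosis, and for none if counted from treatment begun at or after V1. The lag to enrolment therefore alters the routes, timing and probability of the event.

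Bias in the biomarker hazard ratios is conditional: confounding requires that the lag be related to biomarker level, which the document neither shows nor excludes.

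The 81% power is computed correctly. The fall to between 77% and 52% is an illustration for assumed losses of 10% to 50% of expected events, not an estimate; if the 12% already refers to criteria observable within 24 months, there is no loss.

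**What to change.** 1. Reconcile the time windows in the event definition with V1-V5. State when the clock of criterion 3 starts and whether the one-year limit in criterion 1 covers the MGFA IIb part.
2. Fit the Cox models on time since diagnosis with delayed entry at V1, so that patients are compared at the same disease duration. A simpler alternative is to include time since diagnosis at V1 in every model.
3. Record which criterion triggered each event. Report criterion 3 events separately, or add a sensitivity analysis without them.
4. State that the 12% event rate refers to criteria observable within 24 months, or restate the rate and the power.

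The cost is small: the definition and analysis wording, plus one data item for the triggering criterion. Time since diagnosis is already needed to check eligibility. The downside is possibly fewer counted events, a lower stated power, or one extra term in models that have only 8-9 events to support them.

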### Outcome measures

Primary endpoint is the development of a highly active disease course requiring escalation to add-on immunotherapy. Potential prognostic biomarkers (calprotectin, neurofilament light chain, ITIH3, kappa free light chains) as well as temporal differences for immune cell phenotyping, proteome analyses and complement activation profiles (circulating complement activation products and regulatory proteins, including C3b, iC3b, C4b, sC5b-9, Factor H, and Factor I) will be characterized. Secondary endpoints are demographic and clinical differences between highly active and moderate disease course and to assess the risk for myasthenic exacerbation/crisis of gMG patients within two years.

### Data and biosample management

Patient data will be pseudonymized locally on each study site and then be handled in electronic case report forms and submitted electronically via the open-source platform REDCap. The data monitoring committee is represented by [name] and [name], and will work independent of the sponsor. The sponsor of the study has no access to individual patient data. Pseudonymized biosamples will be forwarded for further processing to a biobank, enabling standardized processing and storage until further analysis. Standard operation protocols for biosample handling and shipping are implemented and followed by each study site. Missing data is handled based on the performed analysis, e.g., imputation for proteome analysis.

### Statistical analysis

The study is exploratory, and the number of cases is not sufficient to answer confirmatory questions. The study only serves to discover indications of possible correlations between biomarker levels and outcomes. Overall patient sample size is estimated based on a 10-15% of gMG patients progressing to a highly active disease course within two years for this explorative study [2, 3]. The sample size was calculated using a Cox regression for a *log Hazard Ratio on a covariate* with a standard deviation of 1. A sample size of n=70 provides a power of 81% for a regression coefficient of ≥ 1.099 (corresponding to a hazard ratio of ≥3) at a two-sided significance level of 5%. The calculation assumes an event rate of 12% (n = 8-9). The estimation accounts for potential confounding covariates in a multiple regression analysis, assuming an R^2^ of 0.2. The software nQuery Advisor 9 was used for sample size estimation. Cox proportional hazards models will be used to assess the relationship between biomarkers and disease progression. Time-dependent covariates and potential confounders will be adjusted in Cox regression models. Proteomic data will be analyzed using false discovery rate adjustments for multiple testing. Statistical analysis will be performed by the Institute of Biometry and Clinical Epidemiology Charité - Universitätsmedizin Berlin.

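### The 81% power is a large-sample formula value that is optimistic with 8-9 events: simulating the stated scenario gives about 71-78%, and the hazard ratio of 3 lacks its unit (per 1 SD) in one of the two places it is stated

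*Protocol article*

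**What the plan says.** Protocol article, Methods, *Statistical analysis*: "A sample size of n=70 provides a power of 81% for a regression coefficient of ≥ 1.099", which is described as "corresponding to a hazard ratio of ≥3". The calculation is for a Cox regression on one covariate "with a standard deviation of 1", at a two-sided 5% level, with R² of 0.2 for confounders. On events the text says: "The calculation assumes an event rate of 12% (n = 8-9". The same section bases the sample size on a 10-15% progression rate within two years, plans adjustment for confounders and time-dependent covariates, and calls the study exploratory and too small for confirmatory questions.

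Methods, *Arms and interventions*, gives the same event range ("we anticipate 10-15% of the participants will develop highly active disease") and summarises the calculation as: "Statistical power was calculated to detect hazard ratios ≥3 for biomarkers predicting disease progression". No unit for the hazard ratio is given there.

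**The concern.** Two things make the power statement look stronger than the design behind it.

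- **The formula.** It treats the estimated log hazard ratio as normal, with variance 1/(events × SD² × (1−R²)). That approximation is built for many events and effects close to the null. Here there are 8-9 events, a hazard ratio of 3 per SD and covariate adjustment. The single figure also sits at one point of a 10-15% range.
- **The unit.** A hazard ratio for a continuous marker means nothing without its unit, and the summary sentence under *Arms and interventions* has none.

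At stake is the reading of null results. A candidate marker that misses significance could be set against 81% power and taken to have no prognostic value. If the true power for the target effect is in the seventies, or in the sixties at 10% events, such a marker is missed more often than the text suggests.

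**Working it through.** **Inputs, all from *Statistical analysis*:** n = 70; event rate p = 0.12 (range 0.10-0.15); log hazard ratio β = ln 3 = 1.0986 (1.099 in the text); SD = 1; R² = 0.2; two-sided 5%, so z = 1.96.

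**Step 1. Reproduce the stated figure.** For a continuous covariate in a Cox model:

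Power = Φ( √(n·p·(1−R²)) × SD × β − z )

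- Expected events: 70 × 0.12 = 8.4.
- √(8.4 × 0.8) = √6.72 = 2.592.
- 2.592 × 1.0986 − 1.96 = 0.888, and Φ(0.888) = 81.3%.

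The 81% is confirmed. With exactly 8 or 9 events the formula gives 79.4% or 83.8%.

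**Step 2. Formula over the plan's own event range.**

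- 10%: √5.6 × 1.0986 − 1.96 = 0.640, power 73.9%.
- 12%: 81.3%.
- 15%: √8.4 × 1.0986 − 1.96 = 1.224, power 89.0%.

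The hazard ratio per SD detectable with 80% power is exp[(1.96 + 0.842)/√(n·p·0.8)], that is 3.3, 2.9 and 2.6 at 10%, 12% and 15%. At 10% it lies above the target of 3.

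**Step 3. Simulate the stated scenario.** Assumptions not in the document: normal marker with SD 1, exponential event times, administrative censoring at 24 months, no loss, and 1-3 normal covariates that jointly explain 20% of the marker's variance and have no effect of their own. Separate simulations used 1,500 to 3,000 runs per scenario; at 3,000 runs the Monte Carlo standard error is √(0.73 × 0.27/3000), about 0.8 points.

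| Event rate | Formula | Simulation, across tests and number of covariates |
|---|---|---|
| 10% | 74% | 61-69% |
| 12% | 81% | 71-78% |
| 15% | 89% | 80-84% |

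At 12% the Wald test gives 71-74% and the likelihood-ratio test 75-78%.

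**Step 4. Two checks on the simulation.**

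- Under no effect (12% events, 1 or 3 covariates), the Wald test rejects in 5.1-5.5% of runs and the likelihood-ratio test in 6.3-6.5%. The upper end of the simulated power is therefore slightly flattered.
- With no covariates the simulation gives 79% (Wald) to 81% (likelihood ratio), against 89.0% by formula with R² = 0. The formula is thus already optimistic without adjustment, so the small number of events matters in itself.

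**Step 5. The unit.** *Statistical analysis* sets the covariate's SD to 1, so a hazard ratio of 3 means 3 per 1 SD of one marker. *Arms and interventions* refers to biomarkers in the plural and gives no unit. The two statements describe the same calculation, but only one of them can be interpreted.

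**The case against.** The best defence is that nothing is miscalculated or hidden. Every input to the 81% is disclosed, including the event rate, SD and R², and the study is declared exploratory. A sensitivity table is something that a condensed article may leave to the full protocol. The unit can be recovered from *Statistical analysis*. The simulated figures depend on the choice of distribution, covariates and test. All of this is fair, and it keeps the point to wording. It does not remove it: the published figure is a power for this design, and simulations under the plan's own inputs fall below it at each event rate. The exploratory label restrains claims from positive results; it does not stop a null marker being read against 81%.

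Several stronger readings are tempting, and the document does not support them:

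- *The 81% is wrong arithmetic.* It is reproduced.
- *It holds only at 12% events.* By the formula, power is at least 81% at any rate from 12% upward, and the midpoint of the range (12.5%) gives 82.8%. The 12% is not a favourable choice.
- *Loss to follow-up lowers the power further.* No loss rate is given. If the 12% already means events observed among the 70 enrolled, loss is included.
- *The hazard ratio of 3 compares high with low marker values.* The missing unit invites this, but no dichotomised analysis is planned.
- *The introduction shows that 3 per SD is too large.* It reports a weak correlation for calprotectin but a good one for ITIH3. Correlations with disease activity do not translate into a prognostic hazard ratio per SD.

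**Conclusion.** The point holds as a qualification of the power statement. The 81% is the correct value of a large-sample formula, but at 12% events the design delivers about 71-78%, a shortfall of 3 to 10 points. At the plan's lower rate of 10%, the formula gives 74% and simulation 61-69%; at 15%, the figures are 89% and 80-84%. The simulated values rest on the assumptions in step 3 of the working, and other marker distributions or covariates with effects of their own could shift them. The power applies to one biomarker tested at an unadjusted 5% level, and the missing unit under *Arms and interventions* is a defect of the text as it stands. No part of the design or the planned analysis is invalidated.

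**What to change.** - **Statistical analysis:** state the power as about 71-78% by simulation at 12% events (formula 81%), with the simulation assumptions. Give the formula values of 74%, 81% and 89% at 10%, 12% and 15% events. Say that the figure is for a single biomarker at an unadjusted two-sided 5% level, and whether the 12% is net of loss to follow-up.
- **Arms and interventions:** write *hazard ratio ≥3 per 1 SD of a single biomarker*.
- **Reporting:** give each marker's hazard ratio per SD with its confidence interval, and do not conclude from a non-significant result and the 81% that a marker has no prognostic value. Expressing results per SD matches the planning scale; it does not change the test of a linear term or its power.

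The cost is wording and a less favourable stated power. No patients are added.
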